# Protocol for a multicenter, double-blind, randomized, placebo-controlled phase III trial of the inhaled β2-adrenergic receptor agonist salbutamol for transient tachypnea of the newborn (the REFSAL trial)

**DOI:** 10.3389/fped.2022.1060843

**Published:** 2023-01-12

**Keywords:** transient tachypnea, respiratory distress, persistent pulmonary hypertension, neonate, salbutamol

## Abstract

**Background:**

Transient tachypnea of the newborn (TTN), which results from inadequate absorption of fetal lung fluid, is the most common cause of neonatal respiratory distress. Stimulation of β-adrenergic receptors enhances alveolar fluid absorption. Therefore, the β2-adrenergic receptor agonist salbutamol has been proposed as a treatment for TTN. This study aims to evaluate the efficacy and safety of salbutamol as supportive pharmacotherapy together with non-invasive nasal continuous positive airway pressure (NIV/nCPAP) for the prevention of persistent pulmonary hypertension of the newborn (PPHN) in infants with TTN.

**Methods and analysis:**

This multicenter, double-blind, phase III trial will include infants with a gestational age between 32 and 42 weeks who are affected by respiratory disorders and treated in eight neonatal intensive care units in Poland. A total of 608 infants within 24 h after birth will be enrolled and randomly assigned (1:1) to receive nebulized salbutamol with NIV or placebo (nebulized 0.9% NaCl) with NIV. The primary outcome is the percentage of infants with TTN who develop PPHN. The secondary outcomes are the severity of respiratory distress (assessed with the modified TTN Silverman score), frequency of need for intubation, duration of NIV and hospitalization, acid–base balance (blood pH, partial pressure of O_2_ and CO_2_, and base excess), and blood serum ionogram for Na^+^, K^+^, and Ca^2+^.

**Discussion:**

The Respiratory Failure with Salbutamol (REFSAL) study will be the first clinical trial to evaluate the efficacy and safety of salbutamol in the prevention of persistent pulmonary hypertension in newborns with tachypnea, and will improve short term outcomes. If successful, the study will demonstrate the feasibility of early intervention with NIV/nCPAP together with nebulized salbutamol in the management of TTN.

**Ethics and dissemination:**

The study protocol was approved by the Bioethics Committee of the Medical University of Warsaw, Warsaw, Poland on November 16, 2020 (decision number KB/190/2020). All procedures will follow the principles of the Declaration of Helsinki. The results of the study will be submitted for knowledge translation in peer-reviewed journals and presented at national and international pediatric society conferences.

**Clinical Trial Registration:**

It is registered at ClinicalTrials.gov NCT05527704, EudraCT 2020-003913-36; Protocol version 5.0 from 04/01/2022.

## Introduction

1.

Transient tachypnea of the newborn (TTN) is the most common cause of neonatal respiratory distress. It affects up to 1% of term, 3.5% of late preterm, and more than 10% of preterm infants born at a gestational age of 33–34 weeks (1, 2). TTN results from inadequate absorption of fetal lung fluid (3). Fetal lung fluid is produced by the developing lung epithelium as a result of the active secretion of chloride ions (Cl^−^) and concomitant passive flow of sodium ions (Na^+^) and water into the fetal alveolar space (4). Physiologically, fetal epinephrine produced during labor that acts *via* β2-adrenergic receptors activates Na^+^ channels and triggers fluid absorption (5). The absence of adequate stress or hormonal function, which decreases Na^+^ reabsorption and results in the retention of fetal lung fluid, has been implicated in the pathophysiology of TTN (6). Stimulation of β-adrenergic receptors by β_2_-adrenergic receptor agonists upregulates alveolar epithelial Na^+^ transport (7) and enhances alveolar fluid absorption (8).

The clinical signs and chest radiograph or chest x-ray (CXR) are crucial in the traditional diagnosis of TTN (9). Unfortunately, CXR is a relatively poor imaging technique. Many studies have criticized the poor quality of x-ray images and discrepancies in the exposure parameters (10). Moreover, CXR involves exposing patients to radiation (11). However, with technological progress and the widespread use of digital techniques in radiological diagnostics, the radiation dose required to fix the CXR images is significantly lower than that for “classic” x-ray images using film.

Nevertheless, a newborn baby may have to get several x-ray images taken during hospitalization, which significantly affects the radiation dose. A newborn's high rate of cell division means that such exposure may increase their risk of cancer by two to three times that of the adults receiving a comparable dose of radiation (10). The risk also increases inversely with a child's immaturity. Lung ultrasound (LUS), which does not have radiation risk, is a repetitive bedside instrument. Therefore, it appears to be an ideal choice for the differential diagnosis of respiratory disorders in newborns.

Utilization of LUS in diagnosing lung diseases has gained increasing attention in recent years. At least a few clinical trials have assessed the usefulness of this method in critically ill adults and newborns. Ma et al. (12) and Szymanski et al. (13) showed that the use of LUS in the diagnosis of TTN, compared to chest radiographs, significantly improves the results and justifies its clinical use.

Although TTN is generally considered benign and self-limiting, it can persist and develop into severe conditions requiring respiratory support, such as persistent pulmonary hypertension of the newborn (PPHN) (14, 15). PPHN affects approximately two per 1,000 live births (16, 17). It is a major cause of neonatal death, with a 4%–33% mortality rate (16). Affected individuals often develop long-term impairments such as neurodevelopmental, cognitive, and hearing abnormalities (18). The syndrome is characterized by sustained elevation of pulmonary vascular resistance, leading to extrapulmonary blood shunting from right to left across persistent fetal channels (patent ductus arteriosus and patent foramen ovale), which can cause severe life-threatening hypoxemia and circulatory failure (19). PPHN is diagnosed in both term and preterm infants, and its etiology includes, in addition to TTN, sepsis, meconium aspiration syndrome, congenital diaphragmatic hernia, congenital pneumonia, birth asphyxia, and respiratory distress syndrome (17). Management of PPHN includes sedation, assisted ventilation, surfactants, pulmonary vasodilators, and inotropic agents (20).

Recommendations for the treatment of TTN include non-invasive oxygen support, preferably in an oxygen therapy (accompanied by routine intensive care activities such as continuous cardiopulmonary monitoring, maintenance of a neutral thermal environment, blood glucose checks, and observation for sepsis). However, continuous positive airway pressure (CPAP) has also proven useful in the prophylaxis and management of TTN (21–23).

The routine use of supportive pharmacotherapy in infants with TTN is poorly documented (24). Given the pathophysiology of fetal alveolar fluid retention in neonates with TTN, furosemide, racemic epinephrine, and salbutamol have been studied in the management of TTN (24). A systematic review of the routine use of diuretics in infants with TTN showed that neither oral nor intravenous furosemide was beneficial with respect to the duration of respiratory symptoms or length of hospitalization (25). A pilot study of nebulized racemic epinephrine in neonates with TTN provided no evidence of efficacy (26, 27).

Studies on salbutamol have demonstrated that this β_2_-adrenergic receptor agonist is effective in the treatment of infants with TTN (14, 15, 28, 29). The study by Talaat et al. (29) on 100 infants with TTN showed that nebulized salbutamol reduced the duration of respiratory support and hospitalization. Several clinical parameters improved significantly, and no side effects were associated with the treatment (29). Nonetheless, a recently published systematic review showed limited evidence that nebulized salbutamol reduces the duration of oxygen therapy for TTN, duration of tachypnea, or need for CPAP and mechanical ventilation (30). Summarizing, the possible benefits and safety of salbutamol in infants with TTN have not yet been fully confirmed. To the best of our knowledge, this will be the first study to examine the potential of early intervention with salbutamol to reduce the risk of PPHN (30).

We propose a research protocol to evaluate the efficacy and safety of salbutamol as supportive pharmacotherapy in association with noninvasive nasal ventilation (NIV) to prevent PPHN in infants with TTN.

## Methods and analysis

2.

### Hypothesis

2.1.

We hypothesize that the early use of inhaled salbutamol in addition to nCPAP in neonates diagnosed with TTN prevents the development of PPHN and need for invasive ventilation.

### Trial design

2.2.

This study is designed as a prospective multicenter, double-blind, randomized, placebo-controlled phase III trial. It will include neonates (gestational age of 32–42 weeks) treated in Poland's eight level 2 and 3 neonatal intensive care units.

Parents of neonates diagnosed with TTN within the first 24 h of life will be offered participation in the study. After providing oral and written information about the study, we will ask both parents to provide written consent for the participation of the neonate in the trial.

We have planned to recruit for the study for 24 months, from December 31, 2021 to December 31, 2023.

### Participants, enrolment, randomization, and statistical methods

2.3.

#### Randomization

2.3.1.

After obtaining signed consent from the parents of the neonates for their participation, the participants will be registered and randomized in an electronic research database.

Enrolled infants will be randomly assigned (1:1) to receive nebulized salbutamol with NIV or placebo (nebulized 0.9% NaCl) with NIV. Stratified (according to gestational age: 32 + 0/7 to 34 + 6/7 weeks, 35 + 0/7 to 37 + 6/7 weeks, and 38 + 0/7 to 41 + 6/7 weeks) blocked randomization will be used to ensure homogeneity across treatment groups and sites (Figure 1).

#### Sample size

2.3.2.

A sample size of 506 patients (253 in each group) was estimated to provide 80% power at *α *= 0.05 to detect a difference in the incidence of PPHN between groups, assuming an incidence of 0.1% in the salbutamol group vs. 4% in the placebo group. Assuming a 20% dropout rate (due to the decision of the principal investigator, withdrawal of consent from a parent/legal guardian, or other reasons described in the subsection “Early termination”), the sample size was fixed at 608 patients.

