#### Computational methods

2.3.3.

Descriptive statistics for categorical variables will be presented as numbers, percentages, and relative frequencies, and that for continuous variables as means, standard deviations, medians, ranges, and interquartile ranges. The incidence of PPHN (primary outcome) between the salbutamol and placebo groups will be compared using the chi-square or Fisher's exact test (dependent on observed incidence). Potential determinants of PPHN will be analyzed using a logistic regression method. The secondary endpoint TTN scale will be analyzed using the Mann-Whitney test. Other exploratory analyses will be conducted using the Student's or Mann-Whitney *U* tests for continuous variables and the chi-square or Fisher's exact tests for categorical variables. Multivariate analyses will be conducted using linear or logistic regression methods. The normality of the distribution of the analyzed variables will be assessed using the Shapiro-Wilk test. Further, analyses will be performed using R 4.0.2 (or later) statistical software [R Core Team (2021). R: A language and environment for statistical computing. R Foundation for Statistical Computing, Vienna, Austria. URL: https://www.R-project.org/]. In all analyses, *α *= 0.05 will be set as the level of significance.

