## Discussion

3.

PPHN affects up to 6.8 per 1,000 term or near-term neonates (11). Despite progress in the management of PPHN, the mortality rate is approximately 4%–33% (11). The expected short-term health benefits of salbutamol include a shorter duration of NIV, reduced oxygen concentration in the respiratory gas mixture, and an improved respiratory function according to the modified TTN Silverman scale. The expected long-term health benefits of salbutamol include a reduced risk of PPHN and, consequently, a reduced risk of severe cardiorespiratory failure requiring intensive care (including iNO and ECMO), reduced mortality risk, and reduced risk of long-term outcomes such as cerebral palsy. As previous studies have not reported any safety issues for the treatment of neonates with nebulized salbutamol, it can be concluded that this treatment is likely to be beneficial to this patient group (18, 23, 32). Nevertheless, our study has its limitations that can influence its outcomes. A considerable limitation is associated with the difficult differential diagnosis of TTN and respiratory distress syndrome in neonates with young gestational age. Another one is regarding the definition of pulmonary hypertension that may also bring some that can suggest this disorder but cannot fully diagnose it.

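### The inflation from 506 to 608 covers 16.8% dropout, not the stated 20%; separately, the 80% power applies only to near-elimination of PPHN

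*Protocol article*

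**What the plan says.** Section 2.3.2 (Sample size) of the protocol article gives 506 evaluable infants, 253 per group, which "was estimated to provide 80% power at" a 5% significance level, "assuming an incidence of 0.1% in the salbutamol group vs. 4% in the placebo group". It then assumes 20% dropout, counting investigator decisions, withdrawn consent and the reasons listed under Early termination, and states that "the sample size was fixed at 608 patients". Allocation is 1:1 (2.3.1). The primary comparison is a chi-square or Fisher's exact test, chosen by observed incidence (2.3.3). No source is given for either the 0.1% or the 4%.

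Two background rates appear elsewhere. The Introduction says "PPHN affects approximately two per 1,000 live births" and the Discussion says "PPHN affects up to 6.8 per 1,000 term or near-term neonates". Section 2.9 keeps infants who stop treatment early under follow-up to day 7 of life or discharge, and allows data collected before withdrawal to be analysed.

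**The concern.** Two things stand out, and they should be kept apart.

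First, 608 is not the number that leaves 506 after a 20% loss. Adding 20% to the target is not the same as recruiting enough to lose 20%, so the section's last figure contradicts its own dropout assumption. Anyone planning from it would expect 506 evaluable infants and, on the stated assumption, get about 20 fewer.

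Second, the assumed treated rate is very low. It implies that infants selected for respiratory symptoms, once given salbutamol, develop PPHN at half the rate the article quotes for all live births and about one seventh of the upper figure it quotes for term or near-term infants. If the true benefit is large but less extreme, the 80% figure does not describe the trial's chance of detecting it.

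**Working it through.** **Inputs.** Treated 0.1%, placebo 4%, alpha 0.05, power 80%, 253 per group, 20% dropout, 608 randomised (all 2.3.2); 1:1 allocation (2.3.1); chi-square or Fisher's exact test (2.3.3); background rates 0.2% (Introduction) and up to 0.68% (Discussion). The article does not state whether the test is one- or two-sided; two-sided is assumed.

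**1. Reproducing 506.** The standard two-proportion formula is

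n' = [1.960·√(2·p̄·q̄) + 0.842·√(p1·q1 + p2·q2)]² / (p2 − p1)²

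With p1 = 0.001, p2 = 0.04 and p̄ = 0.0205 this gives (0.3928 + 0.1671)² / 0.039² ≈ 206.1, or 207 per group. With the continuity correction,

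n = (n'/4)·[1 + √(1 + 4/(n'·0.039))]² ≈ 254.8, or 255 per group (510 in all).

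The stated 253 (506) is within 1% of this. Other variants do not match, per group: two-sided unpooled 204, arcsine 137; one-sided 163, or 211 with correction. So 506 is sound given its inputs.

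**2. The dropout step.**

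- 506 × 1.2 = 607.2, rounded up to an even number = 608. This is the route to the stated figure.
- 608 × 0.80 = 486.4, so about 486 remain, or 243 per arm.
- 1 − 506/608 = 16.8%, the largest loss that still leaves 506.
- 506 / 0.80 = 632.5, so 633, or 634 with equal arms.

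**3. What the slip costs at 0.1% versus 4%.**

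| Method | 253 per arm | 243 per arm |
|---|---|---|
| Continuity-corrected formula | 79.7% | 77.7% |
| Uncorrected formula | 87.4% | 86.1% |
| Fisher's exact test, by enumeration | 90.2% | 88.3% |

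**4. What the effect assumption costs.** The relative reduction is 1 − 0.1/4 = 97.5%. Expected events with 253 per arm are 253 × 0.001 = 0.25 on salbutamol and 253 × 0.04 = 10.1 on placebo. Power of the two-sided Fisher's exact test against 4%, by enumeration over both binomial distributions:

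| Treated rate | 253 per arm | 243 per arm | 304 per arm (no loss) |
|---|---|---|---|
| 0.1% | 90% | 88% | 96% |
| 0.2% | 86% | 84% | 93% |
| 0.68% | 63% | 60% | 73% |
| 1% | 48% | 46% | 59% |
| 2% | 18% | 17% | 23% |

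Fisher power falls to 80% at a treated rate of about 0.32% with 253 per arm and 0.28% with 243. The uncorrected chi-square test, also by enumeration, is more powerful but shows the same pattern: with 253 / 243 per arm, 74% / 72% at 0.68%, 61% / 59% at 1% and 26% / 25% at 2%.

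**The case against.** **The slip barely matters, and the loss may not occur.** Much of this stands. The 20% includes early terminations, yet section 2.9 keeps those infants under follow-up to day 7 or discharge. Many could still contribute the primary outcome, so the real loss may be well under 20%. Even at 243 per arm, exact Fisher power at the assumed rates is 88%. What remains is that the section itself counts these infants as dropouts and then inflates by the wrong operation.

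**The background rates are a poor yardstick.** This also stands in large part. The Introduction's figure covers PPHN from all causes, including meconium aspiration, diaphragmatic hernia and asphyxia, which section 2.3.5 excludes. The Discussion's figure is an upper value for term or near-term infants, whereas enrolment starts at 32 weeks. The trial's PPHN definition may also differ from the one behind those rates. They therefore show that 0.1% is optimistic and unsupported, not that it is impossible.

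**Effect size is the sponsor's choice.** True, but a figure below both rates quoted in the same article needs a stated basis, or at least power at milder effects beside it.

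**Stronger readings that a reader might infer.** One is that the whole calculation fails; it does not, because 506 reproduces. Another is that 80% power requires a treated rate half that of all newborns. Under Fisher's exact test it does not: power at 0.2% is still 86% / 84%. Only under the conservative continuity-corrected formula does power fall below 80% there (76% / 74%; 273 per group needed). A third is that the dropout slip causes the shortfall at 0.68%. It does not: power is 63% with the full 253 per arm and 73% with all 304 retained.

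**Conclusion.** The dropout inflation is wrong as written. On the stated 20%, 608 gives about 486 evaluable infants instead of 506; it covers 16.8%, and 20% would need 634. This is a minor error, worth about 2 points of power at the assumed rates. It takes power below 80% only by the continuity-corrected formula, which starts at 79.7%.

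The effect assumption is a separate point with more practical weight. The calculation assumes, but does not need, a treated rate of 0.1%. By Fisher's exact test, 80% power holds up to a treated rate of about 0.3%. Beyond that it drops quickly, to below 50% at 1% and below 20% for a halving of the placebo rate. The documents support calling the assumption optimistic and unsourced; they do not show it to be wrong.

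These figures rest on two-sided testing, a placebo rate of 4%, equal arms and, for 243 per arm, a full 20% loss to the primary analysis. Nothing in the article says how a non-significant result would be interpreted, so no misreading can be charged to it.

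**What to change.** Keep 608 and correct the text of section 2.3.2:

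- Restate the dropout sentence: 608 randomised gives about 486 evaluable infants at 20% dropout, or 506 at 16.8%.
- State that 80% power applies only to near-elimination of PPHN, that is, a treated rate up to about 0.3% against 4% by Fisher's exact test.
- Beside it, give the power at less extreme treated rates, for example 0.2%, 0.68%, 1% and 2%, as tabulated above.
- Give the basis for 0.1% and 4%, or say that they are working assumptions.

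This needs no extra infants and no change to conduct. The cost is that the published figures look less favourable. Raising the target to 634 (26 more infants) would also remove the inconsistency, but it would recover only about 2 points of power and would not address the effect assumption.

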#### Computational methods

2.3.3.

Descriptive statistics for categorical variables will be presented as numbers, percentages, and relative frequencies, and that for continuous variables as means, standard deviations, medians, ranges, and interquartile ranges. The incidence of PPHN (primary outcome) between the salbutamol and placebo groups will be compared using the chi-square or Fisher's exact test (dependent on observed incidence). Potential determinants of PPHN will be analyzed using a logistic regression method. The secondary endpoint TTN scale will be analyzed using the Mann-Whitney test. Other exploratory analyses will be conducted using the Student's or Mann-Whitney *U* tests for continuous variables and the chi-square or Fisher's exact tests for categorical variables. Multivariate analyses will be conducted using linear or logistic regression methods. The normality of the distribution of the analyzed variables will be assessed using the Shapiro-Wilk test. Further, analyses will be performed using R 4.0.2 (or later) statistical software [R Core Team (2021). R: A language and environment for statistical computing. R Foundation for Statistical Computing, Vienna, Austria. URL: https://www.R-project.org/]. In all analyses, *α *= 0.05 will be set as the level of significance.

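### Randomisation is stratified by gestational age but the named two-sample tests ignore the strata; this can cost power for the duration and score outcomes (not for PPHN), and the PPHN logistic model needs a method that copes with an empty salbutamol arm

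*Protocol article*

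**What the plan says.** Section 2.3.1 (Randomization) allocates infants 1:1 in blocks, stratified by gestational age in three bands: 32+0 to 34+6, 35+0 to 37+6 and 38+0 to 41+6 weeks. The stated purpose is that "blocked randomization will be used to ensure homogeneity across treatment groups and sites".

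Section 2.3.3 (Computational methods) then names the tests:
- Primary outcome: the incidence of PPHN "between the salbutamol and placebo groups will be compared using the chi-square or" Fisher's exact test.
- TTN score: "The secondary endpoint TTN scale will be analyzed using the Mann-Whitney test".
- Other outcomes: Student's t or Mann-Whitney for continuous variables, chi-square or Fisher for categorical ones.
- Models: "Potential determinants of PPHN will be analyzed using a logistic regression method", and further multivariable analyses by linear or logistic regression. No covariates are listed, and the fitting method is not given.

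Section 2.3.2 (Sample size) plans 253 evaluable infants per arm (608 randomised, so 304 per arm), "assuming an incidence of 0.1% in the salbutamol group vs. 4% in the placebo group". Duration of NIV and duration of hospitalisation are secondary outcomes in section 2.7.

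**The concern.** Stratified randomisation balances the arms on gestational age. A plain two-sample test takes no credit for that balance. It leaves the between-stratum spread in its error term, although the design has removed that spread from the treatment contrast. The standard error is then too large, and the test rejects too rarely both under the null and under a true effect. How much this matters depends on how strongly the outcome varies with gestational age. Time on NIV and in hospital could plausibly vary a good deal between 32 and 41 weeks. An uncommon binary outcome such as PPHN has little to lose.

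The second issue is the PPHN logistic model. The design expects almost no events on salbutamol. When one arm has none, maximum likelihood gives no finite odds ratio for treatment. If that is discovered after unblinding, the choice of a replacement method is post hoc.

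**Working it through.** **1. The plan's own sample size.** Inputs from section 2.3.2: p1 = 0.04, p2 = 0.001, α = 0.05, power 80%. Sidedness is not stated; two-sided is assumed because the aim is "to detect a difference in the incidence of PPHN between groups".

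With mean p = 0.0205 and difference 0.039:
- n = [1.960·√(2·0.0205·0.9795) + 0.842·√(0.0384 + 0.000999)]² / 0.039² = (0.393 + 0.167)² / 0.001521 ≈ 206, rounded up to 207.
- With continuity correction: (206/4)·[1 + √(1 + 4/(206·0.039))]² ≈ 255.

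This is close to the stated 253 per arm, so the inputs are read correctly.

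**2. PPHN: stratified versus crude test.** Simulation with 20,000 runs, 253 per arm and three equal strata (assumed). Placebo risks across strata ranged from 4/4/4% to 8/3/1%.

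| Test | Power | Rejection under the null |
|---|---|---|
| Crude chi-square | 96% | 4.6–4.9% |
| Stratified Mantel-Haenszel | 96% | 4.7–4.9% |
| Crude Fisher | 90% | 2.8–3.1% |

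Stratifying gains nothing here, and the crude tests hold their level.

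**3. Duration outcomes.** The documents give no durations and no effect size, so all inputs are assumptions: log-normal stay, equal strata, 252–253 per arm, stay 12% shorter on salbutamol, two-sided 5%. Compare within rows only, because the log-SD differs between rows.

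| Median days by stratum | log-SD | Plain Mann-Whitney | Stratified rank test (van Elteren) |
|---|---|---|---|
| 21 / 8 / 4 (steep) | 0.4 | 32% | 94% |
| 12 / 7 / 4 | 0.5 | 53% | 79% |
| 8 / 6 / 4 | 0.5 | 71% | 80% |
| 10 / 7 / 5 (mild) | 0.6 | 56% | 64% |
| 3 / 2.5 / 2 | 0.6 | 63% | 65% |
| equal | 0.5 | 80% | 81% |

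Simulation error is one to two percentage points. The plain test's rejection rate under the null falls from about 4% with no gradient to about 0% with the steep one.

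A hand check with a t-test on log days shows the mechanism. The true difference is −ln 0.88 = 0.128.
- Steep: the within-stratum variance is 0.4² = 0.16, and the variance of ln 21, ln 8, ln 4 is 0.463. The plain test uses SE = √(2·(0.16 + 0.463)/253) = 0.070, but the contrast actually varies with SE = √(2·0.16/253) = 0.036. It needs a difference above 1.96·0.070 = 0.138. Power is Φ((0.128 − 0.138)/0.036) ≈ 39%, against Φ(0.128/0.036 − 1.96) ≈ 95% when stratified.
- Mild: the variances are 0.36 within and 0.080 between, giving SE 0.059 used against 0.053 actual. Power is about 59% plain and 67% stratified.

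Both agree in pattern with the rank-test simulation. The TTN score was not simulated; the same reasoning applies to it in direction, not in size.

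**4. Separation in the PPHN model.** P(no salbutamol events) = (1 − p)^n.

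| Salbutamol rate | n = 253 | n = 304 |
|---|---|---|
| 0.1% (design) | 78% | 74% |
| 0.2% | 60% | 54% |
| 0.5% | 28% | 22% |
| 1% | 8% | 5% |

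With n = 253 it is the majority outcome only below about 0.27% (1 − 0.5^(1/253)). Expected events are 253·0.04 + 253·0.001 ≈ 10.

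Example, 10/253 against 0/253, fitted by maximum likelihood with a treatment term: log odds ratio about −22, SE about 13,600, Wald p = 0.999. On the same data Fisher gives p = 0.0018 and the likelihood-ratio test p = 0.0002.

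**The case against.** The case against is substantial, and several stronger readings fail.

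- A reader might infer that every planned comparison is unstratified. The text does not go that far. The regressions list no covariates and could include gestational age, which is a detail commonly left to the analysis plan. Only the named two-sample tests ignore the strata.
- A reader might infer that the primary analysis is invalid or underpowered for this reason. It is neither, as step 2 shows.
- A reader might infer that the logistic regression will fail. The protocol does not say that treatment is in the model or that the fit is ordinary maximum likelihood; its wording does not exclude a penalised or exact fit. Even with treatment included, only its coefficient and Wald test break down. The other covariates and the likelihood-ratio test remain usable.
- The Introduction's figures for term, late preterm and 33–34 week infants (up to 1%, 3.5%, more than 10%) might be read as proof of a prognostic gradient. They are frequencies of TTN among births, not outcomes among infants who already have it.
- Repeated scoring of the TTN scale might suggest a multiplicity problem. The protocol plans no time-by-time testing, and the time point or summary can be fixed in the analysis plan.
- The phrase about homogeneity across sites is loose, because gestational age is the only listed factor. The passage points to a figure that is not shown, so it cannot be called an error.

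It is also fair to say that the steep example is the most favourable one, and that a conservative test produces no false positives. What the objection does not remove is that section 2.3.3 fixes specific tests that discard the design's stratification, while a stratified test was never materially worse in any scenario.

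**Conclusion.** The point holds in a limited form.

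- **PPHN:** leaving out the strata costs essentially no power, and the crude test remains valid. A stratified estimate there is a matter of consistency with the design.
- **Durations and TTN score:** the named tests are conservative and lose power in proportion to the gestational-age gradient. The loss runs from nothing (80% vs 81%), through modest (56% vs 64%), to severe (32% vs 94%). These figures rest wholly on assumed durations, spread and effect; the documents cannot say where the trial lies in that range.
- **Logistic model:** conditional on treatment being a term and on maximum-likelihood fitting, the treatment odds ratio would be non-finite in 74–78% of trials at the design rate, and in 28% if the salbutamol rate is 0.5% (n = 253).

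The separation figures follow from the protocol's own rates by exact arithmetic.

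**What to change.** State the following in the analysis plan before unblinding:

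1. **Duration of NIV, duration of hospitalisation and TTN score:** compare arms with a test stratified by the three randomisation bands (for example van Elteren), or with regression adjusted for them, in place of the plain Mann-Whitney or t-test.
2. **PPHN:** report a Mantel-Haenszel risk difference stratified by the same bands, with a confidence interval. It remains defined when the salbutamol arm has no events. Present it as analysis following design, not as a gain in power.
3. **PPHN logistic model:** say whether treatment is a term. If it is, specify Firth penalised (or exact) logistic regression with arm and gestational-age stratum only, since about 10 events cannot support a longer covariate list.

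The cost is a few sentences of plan text and a few lines of R. It needs no extra data, no extra patients and no change to the randomisation.
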